### Trial design {8}

This study is a prospective, multicenter randomized, controlled, non-blinded trial. This study evaluates intraoperative irrigation via ACF with a subdural drain versus a subdural drain alone after the evacuation of a CSDH. Except for randomization to irrigation versus no irrigation, the management of the study participants will not differ from the current management of patients. A 1:1 stratified randomization will be performed at each site using a web-based system. Clinical symptoms and imaging assessments will be conducted by the treating physicians at each facility, following the timeline of the participants.

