### Sample size {14}

The present study aimed to recruit 1186 cases, with 593 patients allocated to each group. The target number of cases was determined based on a previous meta-analysis that examined the efficacy of irrigation for CSDH. A meta-analysis reports a recurrence proportion of 8.06% (38/471) in the irrigation group and 13.05% (59/452) in the non-irrigation group; however, this difference was not statistically significant [17]. The 95% confidence intervals were 5.8–10.9% for the irrigation group and 10.1–16.5% for the non-irrigation group. To account for the differences in outcome measures between the prior and present studies, we set the proportions of patients meeting the criteria for ipsilateral reoperation at 7% for the irrigation group and 12% for the non-irrigation group. Using *α* = 0.05 and *β* = 0.20 and accounting for a 10% dropout proportion, a total of 1186 cases, with 593 cases in each group, have been calculated to be necessary for the current study. In determining the sample size, the sample size calculation tool for 2 × 2 contingency tables by Kazuhiko Nagashima was used [35] (https://nshi.jp/contents/js/twofreq/).

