## Statistical methods

### Statistical methods for primary and secondary outcomes {20a}

A statistician blinded to the treatment assignments will perform the analysis. For the primary endpoint, we will adhere to the intention-to-treat (ITT) principle; all patients who have been randomized and underwent surgery will be analyzed according to the group they were allocated to, irrespective of the treatment they received. When outcomes are missing for these patients, they will be treated as not having met the criteria for reoperation. The comparison for this endpoint between the two groups will be made using Fisher’s exact test. As a secondary analysis, the odds ratio estimates and their 95% confidence intervals will be calculated for the primary endpoint and secondary endpoints of the proportion of reoperations, the proportion of deaths, and the proportion of surgery-related complications. For the secondary endpoints of mRS, change in GCS, time from surgery to discharge, and operative time, the two groups will be compared by calculating the mean difference between the groups and its 95% confidence interval. 95% confidence intervals will be calculated using the Clopper-Pearson and bootstrap methods, respectively.

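### The interval method assigned to the odds ratios, Clopper-Pearson, is for a single proportion and gives no confidence interval for a two-arm odds ratio

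*Protocol article*

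**What the plan says.** All the relevant text is in the protocol article, section {20a} on statistical methods.

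- Primary test: "The comparison for this endpoint between the two groups will be made using Fisher’s exact test".
- First group of estimates, which the article labels secondary: "the odds ratio estimates and their 95% confidence intervals will be calculated for the primary endpoint and secondary endpoints of the proportion of reoperations", and also for deaths and surgery-related complications.
- Second group: mRS, change in GCS, time to discharge and operative time are compared by "calculating the mean difference between the groups and its 95% confidence interval".
- Closing sentence: "95% confidence intervals will be calculated using the Clopper-Pearson and bootstrap methods, respectively".

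The section plans no interval for a single arm's proportion, and no other section names an interval method for an odds ratio.

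**The concern.** There are two groups of estimates, two methods, and the word *respectively*. The plain reading gives Clopper-Pearson to the odds ratios and the bootstrap to the mean differences. The second pairing works and the first does not. Clopper-Pearson inverts a one-sample binomial test, so it takes one count and one denominator and returns limits for one proportion. An odds ratio compares two independent arms and depends on two unknown proportions.

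At stake is the reported precision of the treatment effect. The odds ratio is the only effect estimate the article names for the primary endpoint, and the same sentence governs reoperations, deaths and complications. An analyst following the text would have to substitute something. In an open-label trial that substitution is better fixed in writing before the data are seen, and it should not be one that can contradict the primary test.

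**Working it through.** **1. Reproduce the planned size.** Section "Sample size {14}" gives 7% and 12%, α = 0.05, β = 0.20 and 10% dropout. Two-sided, without continuity correction, with mean proportion 0.095:

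n = [1.960·√(2·0.095·0.905) + 0.842·√(0.07·0.93 + 0.12·0.88)]² / 0.05² = [0.813 + 0.348]² / 0.0025 ≈ 539 per arm.

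539 × 1.10 = 592.9, which rounds to the stated 593 per arm. No interval method enters this calculation.

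**2. What Clopper-Pearson does.** For x events in n, the limits are the 2.5% quantile of Beta(x, n−x+1) and the 97.5% quantile of Beta(x+1, n−x). Applied to the meta-analysis counts in the sample size section:

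| Count | Computed | Stated |
|---|---|---|
| 38/471 | 5.77–10.91% | 5.8–10.9% |
| 59/452 | 10.09–16.51% | 10.1–16.5% |

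The article's own per-group intervals agree with Clopper-Pearson, one arm at a time. That is the use the method is built for.

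**3. Illustration at the planned rates.** 0.07 × 593 ≈ 42 events and 0.12 × 593 ≈ 71 events.

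- Odds ratio = (42 × 522)/(551 × 71) = 0.560. Fisher p = 0.0054.
- Exact conditional interval (inverting the noncentral hypergeometric tails): 0.366–0.850.
- Wald interval on the log scale: SE = √(1/42 + 1/551 + 1/71 + 1/522) = 0.204, giving 0.376–0.836.
- Clopper-Pearson: 5.15–9.45% for irrigation and 9.47–14.86% for no irrigation. These are two intervals for two proportions, and neither is an interval for the odds ratio.

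**4. A hypothetical workaround, not in the protocol.** Suppose an analyst divided one arm's odds limits by the other's. The odds limits are 0.0543 and 0.1044 (irrigation), and 0.1046 and 0.1746 (no irrigation).

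- Lower limit: 0.0543/0.1746 = 0.311.
- Upper limit: 0.1044/0.1046 = 0.998.

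Summing exact binomial probabilities over all outcomes at true rates of 7% and 12%:

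| Per arm | Coverage of combined interval | Combined interval excludes 1 | Fisher power | Fisher significant, combined interval includes 1 |
|---|---|---|---|---|
| 593 | 99.6% | 53% | 82% | 28% |
| 534 (about 10% lost) | 99.6% | 47% | 77% | 30% |

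**5. The proposed replacement.** In the same enumeration the exact conditional interval excludes 1 in 81.6% of trials at 593 per arm, the same as Fisher's power, and the two never disagree. Exact agreement depends on equal arm sizes, because the null distribution is then symmetric. With unequal arms small discrepancies are possible.

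**The case against.** **It does not touch the primary inference.** This stands. Fisher's test decides the primary comparison, the article calls the odds ratios a secondary analysis, and neither the test nor the 593 per arm depends on the interval method.

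**It is probably a slip in labelling.** The authors may have meant the exact conditional interval, which uses exact tails in the same spirit and pairs naturally with Fisher. Or they may have meant Clopper-Pearson for per-arm proportions, as in the sample size section. Either is plausible, but the text says neither. In matched-pair data a Clopper-Pearson interval can be transformed into one for an odds ratio. That does not help here, because the arms are independent: "A 1:1 stratified randomization will be performed at each site using a web-based system".

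**A statistician would simply use a proper method.** Likely so, and the standard choices barely differ here (0.37–0.85 against 0.38–0.84). This limits the practical harm but does not make the sentence correct.

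**The SAP may settle it.** The article promises one before data lock, and it may do so. But the article is not silent on the point: it names a method, and that method does not fit the estimate.

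**Stronger readings the documents do not support.** A reader might infer that the trial's interval will cover 99.6% or miss the effect in nearly half of trials. Those figures belong to the workaround in step 4, which the protocol nowhere prescribes. A reader might also infer that the effect analysis needs redesign around an adjusted logistic model or a risk difference. The section contains no adjusted model, and neither change follows from this error.

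**Conclusion.** The sentence is wrong as written: it gives a one-proportion method to a two-arm odds ratio, and nothing else in the article corrects it. It should be fixed, but it does not invalidate the primary analysis. The direct consequence is that the only named effect estimate for the primary endpoint, and the odds ratios for three secondary endpoints, have no usable interval method.

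The realistic cost is an unplanned choice among standard methods, which is small numerically. A literal improvisation could cost more: 0.31–1.00 in place of 0.37–0.85 in the illustration.

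The conclusion rests on reading *respectively* in the order in which the section lists its estimates. The figures assume true rates of 7% and 12% and equal arms.

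**What to change.** Replace the closing sentence of section {20a} with wording to this effect: confidence intervals for odds ratios will be exact conditional intervals, consistent with Fisher's test; intervals for mean differences will use the bootstrap; Clopper-Pearson intervals will be used only if per-arm proportions are reported. Carry the same wording into the SAP before data lock.

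The cost is one sentence. The primary test, sample size, data collection and consent do not change.

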### Interim analyses {21b}

No interim analyses are planned.

### Methods for additional analyses (e.g. subgroup analyses) {20b}

Subgroup analyses or other exploratory analyses may be added if necessary.

### Methods in analysis to handle protocol nonadherence and any statistical methods to handle missing data {20c}

If a significant amount of data is missing for any of the secondary endpoints or other analyses, we will conduct exploratory analyses to assess the impact of the missing data.

### Plans to give access to the full protocol, participant level-data, and statistical code {31c}

The protocol for this clinical trial is publicly available. The data sets and statistical codes analyzed in this study are available from the corresponding author upon reasonable request. Prior to data lock, a statistical analysis plan (SAP) will be established. This plan is essential and will be promptly registered with the jRCT upon completion. All subsequent analyses will be conducted in accordance with this SAP.

## Oversight and monitoring

### Composition of the coordinating center and trial steering committee {5d}

The study is planned, conducted, and coordinated by the Nagoya University research team. Day-to-day support for the study will be provided by the Nagoya University research team’s coordination and management practitioner. The study’s conduct, safety, recruitment, and follow-up are to be reviewed monthly. The data management officer will manage the data appropriately and ensure quality, reliability, and integrity. Additionally, the Nagoya University research team will double-check the investigator’s decisions about whether patients meet the criteria for reoperation, the primary endpoint, before data locking.

### Composition of the data monitoring committee and its role and reporting structure {21a}

A monitor authorized by the Nagoya University School of Medicine will supervise the sources of consent forms and clinical data collected at each facility. Case registration will be temporarily suspended if the number of cases confirmed by monitoring shows discrepancies between the assigned treatment group and the irrigation information collected by REDCap® exceeds 5% of the target number of cases for this trial (59 cases). Subsequently, an independent monitoring committee consisting of three external experts who are not affiliated with this study will be consulted for advice on the feasibility of continuing this trial as well as on measures to prevent noncompliance with the assigned treatment group if the trial is to be continued. The independent monitoring committee has the following three members: [name], Department of Neurosurgery, Aichi Medical University Graduate School of Medicine, Nagakute, Aichi, Japan; [name], Department of Neurosurgery, Nagoya Central Hospital; and [name], Department of Neurosurgery, Aichi Cancer Center Hospital, Nagoya, Japan.

### Adverse event reporting and harms {22}

Expected adverse events include cerebral hemorrhage, ischemic stroke, wound infection, and meningitis, and all other adverse events will be collected. These adverse events will be rated in terms of severity on a 5-point scale from grades 1 to 5 based on the Common Terminology Criteria for Adverse Events (CTCAE). The investigator will immediately report any serious adverse events related to the clinical trial to the hospital director and the investigators managing the study ([name], [name]). Data on all serious adverse events will also be collected in REDCap®. All data on adverse events will be published with the study results.

The principal investigator of the study will consider the continuation or discontinuation of the research under the following circumstances:If a serious adverse event or disease report suggests that continuing the study poses safety concernsIf recruiting participants for the study becomes challenging, making it difficult to achieve the planned number of casesWhen significant new information regarding the quality, safety, or efficacy of the medication and surgical procedure is obtainedIf the certified clinical research review committee directs changes to the research plan and it is deemed difficult to comply with these changes

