### Who will take informed consent? {26a}

In this study, a neurosurgeon, who is also an investigator or subinvestigator, approaches patients who are eligible for CSDH surgery. Following the explanation and consent for surgery, patients are informed about the study. Patients are enrolled in the study only if they consent to both the surgery and the research. If a patient is unable to provide written consent, it will be obtained from their next of kin. Patients who choose not to participate in the study can still receive the same quality treatment as participants. The participants will be free to withdraw from the study at any time in accordance with the most recent 2013 version of the Declaration of Helsinki.

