### Implementation {16c}

Registration and randomization of patients will be performed by the physician at each participating facility when the decision for surgery has been made and consent from the patient or proxy has been obtained. The physician at each site will perform the surgery according to the method allocated in the web system.

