## Assignment of interventions: blinding

### Who will be blinded {17a}

Given the nature of surgical intervention, it is impossible to blind the medical staff involved. Furthermore, since the primary outcome measure is meeting the criteria for reoperation, blinding the participants would be meaningless. Therefore, from the perspective of protecting participants’ rights, participant blinding will not be implemented either.

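### The compared complication endpoint counts only operation-related events in an open-label trial with no independent assessor named, so differing attribution between arms can bias its odds ratio

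*Protocol article*

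**What the plan says.** **Endpoint and analysis.** The list under Secondary endpoints includes complications, restricted to those related to the operation. Statistical methods for primary and secondary outcomes {20a} plans an odds ratio with a 95% confidence interval for "the proportion of surgery-related complications". Six-month mortality is compared in the same way and carries no such restriction.

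**Who is in a position to judge.** Who will be blinded {17a} says that "it is impossible to blind the medical staff involved". Consent is taken by "a neurosurgeon, who is also an investigator or subinvestigator". Under Implementation {16c}, "The physician at each site will perform the surgery according to the method allocated in the web system". Trial design {8} gives clinical and imaging assessment to the treating physicians, and Plans for assessment and collection of outcomes {18a} gives data entry to the site investigators. The section on the coordinating center {5d} describes a central double-check, but only of whether the reoperation criteria were met.

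**What is collected.** Adverse event reporting and harms {22} expects cerebral hemorrhage, ischemic stroke, wound infection and meningitis, and adds that "all other adverse events will be collected", with CTCAE grading. It also states that "Data on all serious adverse events will also be collected in REDCap" and that "All data on adverse events will be published with the study results". Separately, "The investigator will immediately report any serious adverse events related to the clinical trial" to the hospital director and the managing investigators.

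**The concern.** Whether a stroke or an infection occurred is largely a matter of fact. Whether it was related to the operation is an opinion, and here it would be formed by people who know the arm. Both arms have the burr hole and the drain, and irrigation is the only planned difference. A physician may more readily blame the procedure after the added step. A physician who favours irrigation may do the opposite. Either habit makes the share of events that are counted differ between arms.

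Randomisation protects a comparison of all events. It does not protect a comparison of events selected after the fact with knowledge of allocation. A blinded statistician cannot undo a selection already made at the site. At stake is the main non-fatal harm result: a real excess of a named event could be hidden, or a false one created, in a trial that may lead to a recommendation for irrigation.

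**Working it through.** The documents state no complication rate and no attribution rate, so there is no figure of the plan's own to reproduce. All rates below are assumptions. The only planned figure used is 593 patients per arm, from Sample size {14}.

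**Formula.** Let p be the true proportion with an event, equal in both arms, and let a1 and a0 be the shares of events called related in the two arms. The observed proportions are p·a1 and p·a0, and

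OR = [p·a1/(1 − p·a1)] / [p·a0/(1 − p·a0)].

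**Main illustration.** p = 0.06, a1 = 0.80, a0 = 0.50.
- Observed: 0.06 × 0.80 = 0.048 and 0.06 × 0.50 = 0.030.
- OR = (0.048/0.952)/(0.030/0.970) = 0.05042/0.03093 = 1.63. The true value is 1.0.

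**Range.** The last column is the chance, with 593 per arm, that a Wald 95% interval for the log odds ratio excludes 1. The article names other interval methods, so this column is indicative only.

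| True rate, both arms | Called related | Observed | OR | Chance interval excludes 1 |
|---|---|---|---|---|
| 3% | 80% vs 50% | 2.4% vs 1.5% | 1.61 | about 18% |
| 6% | 80% vs 50% | 4.8% vs 3.0% | 1.63 | about 35% |
| 10% | 80% vs 50% | 8.0% vs 5.0% | 1.65 | about 55% |
| 5% | 90% vs 70% | 4.5% vs 3.5% | 1.30 | about 13% |
| 10% | 90% vs 70% | 9.0% vs 7.0% | 1.31 | about 24% |
| 15% | 90% vs 70% | 13.5% vs 10.5% | 1.33 | about 35% |
| 6% | 80% vs 80% | 4.8% vs 4.8% | 1.00 | about 5% |

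**Opposite direction.** Suppose 50% are called related after irrigation and 80% after no irrigation. A true 9.6% with irrigation against 6% without then gives 0.096 × 0.50 = 0.048 and 0.06 × 0.80 = 0.048. The observed odds ratio is 1.0, while the true one is (0.096/0.904)/(0.06/0.94) = 1.66.

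**Why the replacement should not be any serious adverse event.** Sample size {14} plans for 7% and 12% meeting the reoperation criteria, which is 593 × 0.07 ≈ 42 and 593 × 0.12 ≈ 71 patients. If recurrence leading to reoperation is recorded as a serious event (an assumption), a count of all serious events would carry about 30 fewer events in the irrigation arm from efficacy alone. That could mask procedural harm.

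**The case against.** Five points can be made against the concern.

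- **The wording may name a category.** Operation-related complications could mean a fixed list of perioperative events, with no case-by-case causality opinion, and the full protocol or the SAP may define it. A missing definition in a condensed article would not be a finding. What stands is that both places in the article state the endpoint with the relatedness restriction. If a fixed list is meant, the fix merely says so.
- **The surgeon is not named as judge of relatedness.** This is correct. It is an inference from the sections on consent, implementation, blinding and data collection. The supported statement is weaker: no other assessor is named.
- **Nothing is lost.** All adverse events are collected and graded, all serious ones are entered in REDCap, and all adverse-event data are to be published. This is a real mitigation, since readers will be able to see the unrestricted events. It does not make the unrestricted comparison the planned one.
- **Other outcomes are free of attribution.** Mortality is compared directly, and a disabling event would also bear on the mRS and GCS. So the point concerns one endpoint, not the safety assessment as a whole. The Discussion also acknowledges possible bias from lack of blinding in general terms.
- **The magnitude is hypothetical.** It is, and its direction is unknown. At 4.8% against 3.0% with 593 per arm, z is about 1.60 and two-sided p about 0.11, so even the main illustration would not be expected to reach nominal significance. With equal attribution there is no spurious difference.

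A reader might also infer that the immediate-reporting rule distorts the arm comparison or the decision to continue the trial. The text does not support this. The rule concerns notification only. The continuation criterion in the same section refers to serious adverse event or disease reports without a relatedness condition, and {5d} provides for monthly review of safety.

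**Conclusion.** The concern holds for the complication endpoint alone. Its planned odds ratio rests on events filtered by relatedness, in an open-label trial with no independent assessor described for that filter. The bias can go either way. On the assumed rates, and with no true difference, it gives odds ratios of about 1.3 (90% vs 70% attributed) to about 1.65 (80% vs 50%). These figures show what differential attribution could do. They do not predict that it will occur.

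The conclusion assumes that relatedness is judged event by event, by people who know the arm. The article suggests this but does not state it. Mortality and the published adverse-event data are unaffected, and the immediate-reporting rule needs no change on this ground. It is a modest but worthwhile correction, because the data for an attribution-free comparison will already be in hand.

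**What to change.** In Secondary endpoints and in {20a}:

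1. Make the main complication comparison the proportion of patients with any of the four events named in {22} (cerebral hemorrhage, ischemic stroke, wound infection, meningitis) within 6 months of surgery, by allocated arm and regardless of attributed cause. Keep the planned odds ratio and 95% confidence interval.
2. Tabulate all other adverse and serious adverse events by arm. Show recurrence or reoperation of the haematoma separately, so that the efficacy outcome does not enter the harm comparison.
3. Keep the surgery-related count as a supporting tabulation.

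The cost is a change of endpoint wording and additional tables from data already collected. The downside is that some background events in elderly patients will be counted in both arms and will dilute the comparison slightly.
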